## Background

Hepatitis B virus (HBV) infection is a major health problem worldwide with an estimated 350 million chronic carriers [1], and carriers in China account for 33% of all chronic carriers globally [2, 3]. Although treatment of chronic hepatitis B (CHB) has dramatically improved over the past decade, chronic HBV infection is still the most common underlying cause of hepatocellular carcinoma (HCC), which remains one of the most common cancers worldwide. A large longitudinal epidemiological study of the natural history of patients with chronic HBV infection has shown that baseline HBV DNA level or cirrhosis is an independent predictor for the development of HCC [4].

Although antiviral therapy can theoretically prevent HCC by inhibiting HBV replication and preventing the development of, or even reversing, cirrhosis, in patients with fibrosis or cirrhosis, eradication or suppression of HBV does not remove this risk and occurrence of HCC, but can control the complications and gain time to prepare for liver transplantation [5–7]. Antiviral therapy has minimal side effects and sustained suppression of HBV replication can be achieved, thus preventing such complications. However, patients with CHB treated with nucleos(t)ide analogs (NUCs) retain a higher risk for HCC compared with patients with inactive stage disease [8].

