Secondary end points are disease progression and overall survival rate. Disease progression is defined as either histological progression reflected by an increase in METAVIR score of at least 1 point or clinical progression reflected by the occurrence of decompensated cirrhosis. Decompensated cirrhosis is defined by the development of complications of portal hypertension (ascites, variceal hemorrhage, hepatic encephalopathy or spontaneous bacterial peritonitis) and/or liver insufficiency (jaundice). Following previous studies [20, 21], liver biopsies are collected at three defined time points: before the start of randomization (unless a biopsy has been performed within 3 months of randomization), at week 72 of the double-blind treatment and at month 24 of the open-label treatment during follow-up. Every patient with liver biopsy of at least six portal tracts is included in the study. To ensure the quality of liver tissue specimens for pathological assessment, liver biopsies in all centers is performed using unified 16G liver biopsy needles and a modified Jamshidi Menghini needle (Allegiance Corporation, McGaw Park, IL, USA), and the tissue is fixed in formalin and embedded in paraffin. Two independent third-party pathologists who are unaware of the patients’ treatment assignment, biopsy sequence and clinical outcome will examine all biopsy slides.

Hepatic fibrosis is assessed by the METAVIR system for fibrosis stage and necroinflammatory activity as a hard index [22, 23]. The fibrosis stages are: no fibrosis (F0), mild fibrosis (F1), moderate fibrosis (F2), severe fibrosis (F3) and cirrhosis (F4). Necroinflammatory activity is: no activity (A0) mild activity (A1), moderate activity (A2) and severe activity (A3). Serum fibrosis biomarkers including Fibrotest, aspartate aminotransferase to the platelet ratio index (APRI), liver stiffness spleen diameter to platelet ratio score (LSPS), and FibroMeters and FibroScan are used to assess hepatic fibrosis as a surrogate index [24, 25]. Hard and surrogates indexes are evaluated at all three time points (baseline, week 72 and week 96 after the open label) for each patient. Changes in liver fibrosis from baseline to weeks 72 and weeks 96 after the open label are analyzed on available pooled data using the METAVIR scoring system and the surrogate index.

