### Participants and eligibility

Inclusion criteria are as follows: (1) men or women aged 18 to 65 years; (2) persistent serum HBsAg for ≥6 months; (3) serum HBV DNA ≥2000 IU/mL or ≥10,000 copies/mL; (4) baseline liver fibrosis (liver biopsy) stage F ≥2 (METAVIR system); (5) TCM syndrome type: blood stasis, or blood deficiency with toxic heat retention and (6) no antiviral or antifibrotic therapy for 6 months. Patients are excluded if they have any of the following at enrollment: (1) history of concurrent malignancy, including HCC; (2) baseline liver fibrosis (liver biopsy) stage F <2 (METAVIR system); (3) immunosuppression (organ transplantation or immunosuppressant use); (4) severe alcoholism; (5) serious uncontrollable heart, kidney, lung, endocrine, blood, metabolic or gastrointestinal primary disease, or mental illness; (6) pregnancy or lactation; (7) allergic constitution or allergic to TCM use; (8) no prescribed medication, poor compliance, incomplete data affecting the efficacy and safety of those judgments; (9) unsuitable for this trial according to the researchers or (10) co-infection with hepatitis C or D virus or HIV.

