### Randomization

This study has two arms. Once enrolled, participants who meet the inclusion criteria are informed about the study and treatment plan. Written informed consent is obtained when the patient accepts this plan and is willing to participate. A consecutively numbered envelope is unsealed by a research assistant. The sealed numbers are generated by a computerized random number generator with SAS software by Boao Tong Medical Technology Co Ltd (Beijing, China) and are concealed and disseminated using opaque envelopes. Based on this number, the patient is randomly assigned in a 1:1 ratio to the treatment group (ETV + RGT, *n* = 500) or control group (ETV + RGT-dummy agent, *n* = 500).

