### Statistical methods

The randomized subjects who have taken at least one dose of study drug and are evaluated for at least once curative effect after taking medication, constitute the full analysis set and safety analysis set. Those who complete all the visits comprise the per-protocol set. The statistical analysis will be performed using SAS 9.1 software (SAS Institute, Cary, NC, USA). The overall loss rate due to adverse events of each group will be calculated. When subjects enter the trial, they are assessed for demographic data, baseline condition and other essential information and are compared between groups. Cumulative incidence of HCC and overall survival rate will be determined by Kaplan–Meier analysis, and the log-rank test will be used for treatment comparisons. Changes from baseline in liver histology (METAVIR score) as well as in liver and spleen imaging (type B ultrasound) between the two groups will be compared by the Cochran–Mantel–Haenszel test. Changes from baseline in serum markers for liver fibrosis and liver function, transient electrograph (FibroScan) and TCM syndrome between the two groups will be compared by a covariance or non-parametric test. The statistical significance is defined as a two-sided *P* <0.05.

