## Discussion

HBV is a common infection that is associated with a considerable burden of liver-related morbidity and mortality worldwide [28]. HBV is strongly associated with HCC by its presence in tumor cells and by the role of persistent HBV infection as a risk factor for the development of HCC [29]. Recent advances have seen the introduction of drug therapy with the potential to have a significant impact on the incidence of liver-related complications [28]. In particular, treatment of CHB has dramatically improved over the past decade [30–32], but persistent HBV infection is still the most common underlying cause of HCC, which remains one of the most common cancers worldwide [33]. Cirrhosis and persistently high viremia are both important risk factors for HCC in patients with CHB [4, 33, 34]. Therefore, antiviral therapy could theoretically prevent HCC by inhibiting HBV replication and preventing the development of, or even reversing, cirrhosis [30–32]. Antiviral therapy alone does not remove this risk and occurrence of HCC [7]. However, it has not been demonstrated whether a combination of TCM and antiviral therapy could have a role in preventing or delaying the development of HCC in patients with CHB.

Clinical trials have been carried out to evaluate the role and efficacy of RGT for HBV-related hepatic fibrosis and compensated cirrhosis [10, 15–18]. RGT administered to block and reverse hepatic fibrosis in CHB or HBV-related compensated cirrhosis is considered one of the treatment options for patients with hepatic fibrosis. Only limited data are available about the effects of RGT blockade and reversal of hepatic fibrosis on the development of HCC in patients with CHB. To date, there have been no RCTs comparing the effects of combined application of RGT and NUCs with NUCs alone on the development of HCC in patients with CHB or HBV-related compensated cirrhosis.

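### The HCC comparison is planned as an unstratified log-rank test although cirrhosis and HBV DNA are named as HCC predictors and known at entry; stratifying would be a small, free gain

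*Protocol article*

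**What the plan says.** **HCC and survival analysis.** Statistical methods plans Kaplan–Meier curves for HCC incidence and overall survival, and "the log-rank test will be used for treatment comparisons". It names no stratum, covariate or Cox model for these outcomes.

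**Allocation.** Under Randomization, "The sealed numbers are generated by a computerized random number generator with SAS software", and on that number "the patient is randomly assigned in a 1:1 ratio to the treatment group" or to control, 500 per arm. No stratification factor is mentioned.

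**Prognostic factors.** The Background reports that "baseline HBV DNA level or cirrhosis is an independent predictor for the development of HCC". The Discussion repeats the point: "Cirrhosis and persistently high viremia are both important risk factors for HCC in patients with CHB".

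**Population.** Entry requires "baseline liver fibrosis (liver biopsy) stage F ≥2 (METAVIR system") and "serum HBV DNA ≥2000 IU/mL or ≥10,000 copies/mL". Patients from F2 to F4 are therefore mixed, HBV DNA has no upper limit, and both values exist for every patient before randomization.

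**Histology.** METAVIR change from baseline is compared by the Cochran–Mantel–Haenszel (CMH) test, with no stratum named. For the secondary end point, "Disease progression is defined as either histological progression reflected by an increase in METAVIR score of at least 1 point" or as clinical decompensation. F4 is the top of the fibrosis scale.

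**The concern.** The article relies on cirrhosis and viral load as drivers of HCC, and collects both at entry, but as described neither the allocation nor the HCC test uses them. Two things follow. First, when patients of very different risk are pooled, the hazard ratio that an unstratified log-rank test detects is pulled slightly towards 1, and some power is lost. Second, if one arm happens to receive more cirrhotic patients, the unstratified hazard ratio moves with that imbalance. The article says that baseline condition will be compared between groups but not what follows if it differs. An adjustment chosen after seeing such a difference would be less convincing than one fixed beforehand.

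The histology test has a related weakness. How far a patient can move on the METAVIR fibrosis scale depends on the starting stage: an F2 patient can rise two stages, an F3 patient one, an F4 patient none. A test without baseline stage as a stratum pools patients for whom a rise in stage is possible with patients for whom it is not.

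**Working it through.** **No figure in the plan to reproduce.** The Sample size section rests on fibrosis reversal (39% versus 61%), not on HCC. The article gives no HCC rate, HCC hazard ratio, share of F4 patients or prognostic strength. From the article: 500 per arm and two-sided 0.05. Everything else below is an assumption, shown over a range.

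**1. Size of a chance imbalance in cirrhosis.** Assume 40% F4.
- SD of the between-arm difference = √(2 × 0.4 × 0.6 / 500) = 0.031, or 3.1 points.
- A 2-SD imbalance is 6.2 points, that is 43.1% versus 36.9%.

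**2. Effect on the hazard ratio.** If F4 carries k times the risk, the approximate shift is (1 + (k − 1) × 0.431) / (1 + (k − 1) × 0.369).

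| k | Calculation | Shift |
|---|---|---|
| 3 | 1.862 / 1.738 | 1.07 |
| 4 | 2.293 / 2.107 | 1.09 |
| 5 | 2.724 / 2.476 | 1.10 |

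**3. Scale against sampling error.** The standard error of the log hazard ratio is about 2/√d for d events: 0.28 at 50 events and 0.20 at 100.
- Smallest case (k = 3, 50 events): ln 1.07 = 0.07, and 0.07 / 0.28 is about 0.25 standard errors.
- Largest case (k = 5, 100 events): ln 1.10 = 0.095, and 0.095 / 0.20 is about 0.5 standard errors.

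**4. Power and type I error, stratified by cirrhosis and by high/low HBV DNA.** Simulation with 1,000 patients, 5 years of follow-up, treatment HR 0.5, 40% cirrhosis, 50% high HBV DNA and 3,000 runs per scenario. Entries are power in %, unstratified → stratified.

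| Control 5-year risk | Prognostic HRs 2 and 1.5 | 3 and 2 | 5 and 3 |
|---|---|---|---|
| 5% | 53.6 → 54.2 | 52.8 → 53.5 | 52.6 → 54.1 |
| 10% | 83.2 → 83.5 | 83.2 → 84.0 | 81.2 → 84.4 |
| 20% | 98.9 → 98.9 | 98.4 → 98.5 | 97.6 → 99.0 |

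The gain is 0 to about 3 points and exceeds 1 point only with the strongest predictors. With no treatment effect, both tests rejected in 4.1% to 5.7% of runs, which is 5% within simulation error.

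**5. Power, stratified by F4 alone.** A second simulation used HR 0.55, F4 risk ratios of 5 to 8, 61 to 150 events, 4 years and 2,500 runs each. Power rose from 61.8 to 63.3, 84.6 to 87.0, 74.6 to 78.0 and 91.0 to 94.5, so by 1.5 to 3.5 points. These are strong assumptions, and they set the upper end of the range.

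**6. Histology.** The Sample size section expects at most 45% of patients to have a second biopsy: 0.45 × 500 = 225 per arm. With 40% F4, the SD of the between-arm difference in F4 share is then √(2 × 0.4 × 0.6 / 225) = 0.046, or 4.6 points, from chance alone. This subset is also formed after randomization, so balance on stage is less assured than in the full trial.

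**The case against.** The strongest reply is that nothing in the article is false or contradictory here. Strata and covariates are commonly settled in the analysis plan, which is not shown and may already name them. That stands, and it is why this is a suggestion rather than an error. It does not remove the point, because the article does name the HCC test and allows a covariance analysis for serum markers and FibroScan without doing the same for HCC.

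Several stronger readings are tempting, and the document does not support them:
- **That the log-rank test is biased or invalid.** Under randomization it is neither. Chance imbalance is already part of its sampling error.
- **That all treatment comparisons ignore baseline.** METAVIR and imaging are analysed as change from baseline by CMH, a test that can take strata, and serum markers and FibroScan as change from baseline with a covariance analysis as one option. Only the log-rank test has no baseline element at all.
- **That the protocol names fibrosis stage as the predictor.** It names cirrhosis and HBV DNA. The Background statement also comes from a natural-history study, whereas every patient here receives entecavir, so the strength of baseline HBV DNA under treatment is unknown.
- **That nearly all HCC events will arise in F4 patients.** With 40% F4 the share is 0.4k / (0.4k + 0.6): 67% at k = 3, 77% at k = 5 and 84% at k = 8.
- **That F4 patients cannot progress.** They cannot rise on fibrosis stage, but an increase in necroinflammatory activity or a decompensation still counts. A one-point improvement is open to every enrolled stage.
- **That a promised HCC power is lost.** None is stated.

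**Conclusion.** The point holds as a minor, cost-free improvement. The HCC comparison as described uses neither of the two predictors that the article names, although both are available at baseline for every patient. The consequence is limited: type I error is kept, about 0 to 3.5 points of power are given up, and a 2-SD imbalance in cirrhosis would move the hazard ratio by about 7 to 10%, which is a quarter to a half of its standard error at 50 to 100 events. These sizes rest on assumed values for the F4 share (40%), the risk ratio for cirrhosis (3 to 5 for the imbalance, 2 to 8 for power), the event rate and the treatment effect, none of which the article gives. For histology, the reason to stratify is interpretability: baseline stage decides whether a rise in fibrosis stage is possible. It is not a reason to call the between-arm test biased.

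**What to change.** In the analysis plan, before unblinding and before any unblinded interim look:
1. Make the primary comparison a log-rank test stratified by baseline cirrhosis (F4 versus F2–F3).
2. Give the supporting estimate from a Cox model stratified by F4 with baseline log10 HBV DNA as a covariate, and say that this hazard ratio is a within-stratum one.
3. Keep the unstratified log-rank test as a sensitivity analysis.
4. Stratify the CMH test of METAVIR change by baseline stage (F2, F3, F4), and report progression in F4 patients separately, since for them only activity or decompensation can count.

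If the existing analysis plan already does this, confirming it is enough. The cost is wording only: no new data, no change to the randomization and no change to the sample size.

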**Methods/design:**

This multicenter, centrally randomized, double-blind, placebo-controlled, parallel-group study is planned to complete within 5 years. For the study, 1,000 with CHB or HBV-related compensated cirrhosis are randomly assigned in a 1:1 ratio to a treatment group (0.5 mg ETV once daily; 2 g RGT three times daily) or a control group (0.5 mg ETV once daily; 2 g RGT dummy agent three times daily). The primary end points are the development of HCC and liver-related death. Secondary end points include disease progression and overall survival.

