Although some studies have concluded that RGT can block and reverse hepatic fibrosis in CHB, there are limited data on preventing or delaying the development of HCC in the treatment of CHB or HBV-related compensated cirrhosis. To address this issue, we are conducting a large, prospective, multicenter, centrally randomized, double-blind, controlled trial to establish whether RGT can prevent or delay the development of HCC by blocking and reversing hepatic fibrosis in CHB or HBV-related compensated cirrhosis. The aims of this clinical trial are: (1) to evaluate the effect of combined application of RGT and entecavir (ETV) on development of HCC in patients with CHB or HBV-related compensated cirrhosis and (2) to evaluate the efficacy of combined application of RGT and ETV in preventing or delaying the incidence of decompensated cirrhosis and disease progression in the treatment of patients with CHB or HBV-related compensated cirrhosis.

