### Sample size

We assumed that the rate of hepatic fibrosis reversal would be 39% in the ETV-treated patients at the end of 2 years [26, 27], and 61% in the RGT-treated patients. Using PASS 2002 statistical software (NCSS, Kaysville, UT, USA), we calculated that we need two groups of 186 cases, and each group needs to enroll 223 cases if there is a drop-out rate of 15%, that is, a total of 446 cases. Currently, up to 45% of all enrolled patients will be accepted for a second liver biopsy. A total of 500 cases is required in each group to achieve a power of 0.80 and a significance level of 0.05 in assessing the difference between the two groups.

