The present clinical trial introduces promising and classical herbs and formulae into the treatment of hepatitis-B-related hepatic fibrosis and compensated cirrhosis. Above all, this clinical study evaluates for patients with CHB or HBV-related compensated cirrhosis: (1) the efficacy of TCM (RGT) in preventing or delaying the occurrence of HCC, (2) the efficacy of RGT in reducing the development of decompensated cirrhosis and disease progression for patients with CHB or HBV-related compensated cirrhosis and (3) whether TCM treatment improves the hepatic microenvironment and reduces the development of HCC.

In summary, the results of the present trial are of value because they will provide an important evidence base for the effects of TCM blockade and reversal of hepatic fibrosis on development of HCC for patients with CHB or HBV-related compensated cirrhosis.

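### HCC and liver-related death are both called primary, but the plan does not say whether they form one test or two, or whether either alone is enough; if either is, the false-claim rate is about 0.07 to 0.10, not 0.05

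*Protocol article*

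**What the plan says.** The abstract of the protocol article sets the hierarchy: "The primary end points are the development of HCC and liver-related death. Secondary end points include disease progression and overall survival". The two primary end points are in the plural and joined by *and*.

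The Study design section (the paragraph after Figure 1) keeps the plural but joins HCC and liver-related mortality by *or*. It defines liver-related mortality as death from hepatic decompensation or from HCC, so the two end points share some events.

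The Statistical methods section names Kaplan–Meier and log-rank for the cumulative incidence of HCC and for overall survival. It names no test for liver-related death and none for a composite. It closes with one threshold for everything listed: "The statistical significance is defined as a two-sided" P below 0.05.

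The Sample size section is planned "to achieve a power of 0.80 and a significance level of 0.05 in assessing the difference between the two groups", but the difference in question is fibrosis reversal (39% against 61%), which is not a primary end point. It therefore does not show which primary result decides the trial.

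**The concern.** The choice of primary test and the rule for success are what a 5% error rate refers to. Here two events carry the primary label, one threshold applies to each comparison, and no sentence says how the results combine. Someone following the text could test HCC and liver-related death separately, each at 0.05, and report success if either is significant. The error rate of that conclusion is above 0.05.

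The two results may also disagree. If HCC shows a difference and liver-related death does not, or the reverse, the plan gives no answer on whether RGT succeeded. A rule chosen after the results are known cannot control the error rate.

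**Working it through.** **Step 1. Readings that the text allows.**

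| Reading | Primary tests | False primary claim, no effect on either |
|---|---|---|
| A. One composite, first of HCC or liver-related death | 1 | 0.05 |
| B. Two separate tests, either suffices | 2 | above 0.05 (step 2) |
| C. Two separate tests, both required | 2 | at most 0.05 |
| D. HCC alone is tested, as the named log-rank test suggests | 1 | 0.05, but liver-related death then has no role although it is called primary |

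The word *or* in Study design favours A. The plural in both places, the *and* in the abstract and the log-rank test on HCC alone count against A. Nothing in the text separates B from C.

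**Step 2. Size under reading B.**

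Inputs: two tests, each at two-sided 0.05 (Statistical methods); RGT has no effect on either end point; approximately normal test statistics; one final analysis. The plan states no family-wise error rate to reproduce. Its only figure is the 0.05 per test.

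Independent tests: 1 − (1 − 0.05)² = 1 − 0.9025 = 0.0975.

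Correlated tests: P(at least one) = 0.05 + 0.05 − P(both). The joint probability comes from a bivariate normal with correlation ρ and cut-off |Z| > 1.96. The documents give no ρ, so a range is shown. Positive values are plausible because an HCC death counts towards both end points.

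| Assumed ρ | P(at least one) | P(both) = 0.10 − P(at least one) |
|---|---|---|
| 0 | 0.0975 | 0.0025 |
| 0.5 | 0.091 | 0.009 |
| 0.8 | 0.078 | 0.022 |
| 0.9 | 0.071 | 0.029 |

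Whatever the correlation, the rate cannot exceed 0.05 + 0.05 = 0.10. At ρ = 0.5 it is 0.091 / 0.05 = 1.8 times the stated level. Even at ρ = 0.9 it is 0.071 / 0.05 = 1.4 times.

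If only false claims in favour of RGT count, the nominal level is 0.025 and independent tests give 1 − 0.975² = 0.049, again about double.

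**Step 3. Check of the remedy.**

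A single composite test has an error rate of 0.05 by construction. Under Holm, a first false claim needs the smaller P value to be at or below 0.025. With no effect on either end point, that has probability at most 0.025 + 0.025 = 0.05 at any correlation, and 1 − 0.975² = 0.049 if the tests are independent.

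The power of either option cannot be computed, because the plan gives no event rate or effect size for HCC or liver-related death.

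**The case against.** The strongest reply is that Study design, with its *or*, describes one composite, so there is nothing to split. That reading is possible and would remove the inflation. It does not settle the text, because the end points stay plural in both places, time to first event is never defined, and the log-rank test is assigned to HCC and to overall survival rather than to a composite. If a composite was meant, the wording still has to be corrected.

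A second reply is that Statistical methods names no test for liver-related death, so counting two primary tests is itself an interpretation. That is correct, and it is why the inflated figure is conditional on reading B.

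A third is that multiplicity belongs in an analysis plan that is not shown. For secondary and exploratory measures this stands. It is weaker for the primary end point, which this article does state, and states in two different ways.

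A reader might infer more than the documents support:

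- *All four end points form one family*, with a rate of about 0.16 at an assumed correlation of 0.5. The plan labels two as primary and two as secondary, which is a ranking. Pooling them ignores it, and no test is named for disease progression as defined.
- *The HCC and progression aims are co-equal.* The Background numbers a second aim, "to evaluate the efficacy of combined application of RGT and ETV in preventing or delaying the incidence of decompensated cirrhosis and disease progression", beside the HCC aim, and the Discussion repeats it. Numbering gives no rank, but neither does it cancel the primary and secondary labels.
- *The fibrosis measures add a further family*, with a rate of about 0.32 for twelve tests at the same assumed correlation. Study design says that changes in fibrosis "are analyzed on available pooled data using the METAVIR scoring system and the surrogate index". It does not make each index an end point or say that each would support a claim of efficacy.

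The order of the secondary end points, and the labelling of exploratory measures, can properly be left to the analysis plan.

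**Conclusion.** The point holds for the primary end points only. The article names two, joins them in two different ways, sets a flat two-sided 0.05 and gives no success rule. If they are tested separately and either result suffices, the false-claim rate is 0.0975 at independence, 0.091 at an assumed correlation of 0.5 and about 0.07 at 0.9, and never above 0.10. If they form one composite, or if both must be significant, there is no inflation; the defect is then that the text does not say so.

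The figures assume no effect on either end point and one final analysis. They do not include interim looks, which are a separate matter. This should be corrected before anyone sees unblinded results, but it does not by itself undermine the design.

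**What to change.** In the abstract, in Study design and in Statistical methods, use one wording. The simpler option is a single primary test: time to first HCC or liver-related death, RGT plus ETV against ETV plus dummy, by log-rank at two-sided 0.05, with HCC and liver-related death each reported as components. If two separate primaries are kept, test them by Holm: the smaller P value at 0.025 and, if that is significant, the other at 0.05. In either case, name the test for each primary end point.

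Add one sentence stating that a significant secondary or histological result does not establish efficacy if the primary fails.

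The cost is a few sentences, with no extra patients, visits or procedures. The small downside is that a nominal P below 0.05 on one component or on a secondary end point can no longer stand as proof.
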